#### **9.5 Data Safety Monitoring Board (DSMB) / Safety Committee**

A DSMB is not needed. This study is considered a negligible-risk study: there is a small chance of damage and damage is expected to slight. Therefore, an internal monitor will be used who has completed the basic training for monitors in the UMCG. Monitoring will be performed by an independent monitor.

## 10. STATISTICAL ANALYSIS

Baseline characteristics, primary outcomes and secondary outcomes are quantitative and will be presented categorical and continuous. Categorical variables will be presented as absolute numbers and percentages of the total. Continuous variables will be tested for normality using Kolmogorov-Smirnov analysis. Continuous variables will be presented as means and standard deviations for normally distributed data, and medians and interquartile ranges for data that is not normally distributed. Between-group mean (or median) differences, rate differences and rate ratios with 95% confidence intervals (or ranges) will be calculated.

Missing values will be handled using multiple imputation, assuming that there is only missingness at random, and all analyses will be performed on an intention-to-treat basis. The missingness at random assumption will be tested by exploring patterns of missing data using missingness patterns plots and missingness indicators, as well as performing the Little's MCAR test. If the missingness at random assumption had been violated, we will perform Heckman regression.

Intercurrent events may affect the estimated treatment effect. An expected intercurrent event is non-adherence to the study intervention or the use of certain foods or medications outside the advice given by the dieticians. In the case of non-adherence to the study intervention or the use of certain foods or medications, a 'treatment policy' strategy will be used in which we accept that this intercurrent event is part of the intervention and we expect that non-adherence to the intervention also occurs in daily practice. Loss of follow-up because participants decide to stop the study is in our opinion not an intercurrent event but a 'missing data' problem.

SPSS version 28.0 (SPSS Inc., Chicago, IL, USA) will be used for all statistical analyses.

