### 10.1 Primary study parameter(s)

The primary outcome will be adverse events (intra- and postoperative complications and (chemo)radiotherapy toxicity). Relevant complications include hemorrhage, infection and wound healing disorders including dehiscence and fistula. Complications will be measured within 30 days after surgery using the Clavien-Dindo classification and evaluated during hospital stay and planned and unplanned outpatient visits [22]. Clavien-Dindo grade  $\geq 2$  complications will be deemed clinically relevant. Toxicity will be evaluated using the Common Terminology Criteria for Adverse Events (CTCAE), version

4.0, 6 and 12 weeks after the start of (chemo)radiotherapy. The following domains are scored within the CTCAE: xerostomia, taste, throat pain, oral pain, general pain, dysphagia, hoarseness and mucositis. Clinically relevant toxicity will be defined as CTCAE toxicity grade  $\geq 3$ , irrespective of the mentioned domains.

For analysis of between-group differences in the primary outcome, a logistic regression analysis will be performed. The endpoints complications and toxicity will be dichotomized. In case of unbalance between the intervention and the control group, adjusted logistic regression analyses will be performed. A  $p$ -value  $< 0.05$  will be considered as statistically significant.

Subgroup analyses will be performed using the following variables:

- (intended) type of treatment (surgery versus (chemo)therapy)
- Subsite (larynx versus hypopharynx versus oropharynx versus oral cavity)
- Skeletal muscle mass (LSMI in  $\text{cm}^2/\text{m}^2$ )
- Duration of nutritional prehabilitation intervention
- Number of dietetic consultations
- Dietary intake using 24-hour recall

These variables will be added to the regression analyses

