## **10.2 Secondary study parameter(s)**

Secondary outcome measures will be patient-reported quality of life outcome measures (i.e., the EAT-10, EORTC H&N35 and EORTC C30 questionnaires), recurrence and (disease-specific and overall) survival. Patients will be monitored for two years with intervals of at least three months. For further analyses of between-group differences in these secondary outcomes, logistic regression analyses will be performed for categorical outcomes, cox proportional hazard regression for time-dependent outcomes (i.e., recurrence and survival) and linear regression analyses for continuous variables. A  $p$ -value  $< 0.05$  will be considered as statistically significant.

To correct for false discovery rate, the Benjamini-Hochberg procedure will be applied.

Furthermore, an economic evaluation will be performed to compare the incremental cost-effectiveness of nutritional prehabilitation as compared to standard care. A cost-utility analysis (CUA) and cost-effectiveness analysis (CEA) will be conducted from a societal perspective. The CUA will be performed based on EQ-5D-5L defined utilities over a time

horizon of one year. The CEA will incorporate the highest measured grade of complications (Clavien-Dindo classification) at 30 days postoperatively or (chemo)radiotherapy toxicities (CTCAE) at 6 and 12 weeks after the start of (chemo)radiotherapy. Health care consumption will be measured on a patient level and registered on a case-report form and partly on questionnaires (iMCQ items). Productivity losses will be measured using the iPCQ. Costs will be calculated according to the Dutch guidelines for costing research in health economic evaluations, issued by the National Healthcare Institute [39]. There will be no discounting since the time horizon of the analyses does not exceed one year. Cost-effectiveness planes and acceptability curves will be plotted and 95% confidence intervals will be based on bootstrapping.

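### Section 10 allows a range in place of a 95% confidence interval for between-group differences, which affects the continuous secondary outcomes

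*Protocol*

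**What the plan says.** The first paragraph of section 10 covers baseline characteristics and also the primary and secondary outcomes. It makes three statements in sequence:

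- a test: "Continuous variables will be tested for normality using Kolmogorov-Smirnov analysis";
- a rule for description: "Continuous variables will be presented as means and standard deviations for normally distributed data, and medians and interquartile ranges for data that is not normally" …;
- a statement on treatment effects: "Between-group mean (or median) differences, rate differences and rate ratios with 95% confidence intervals (or ranges) will be calculated".

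The third statement offers two contrasts (mean or median) and two kinds of interval (confidence interval or range). It gives no rule for choosing between them.

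Section 10.2 lists among the secondary outcomes "patient-reported quality of life outcome measures (i.e., the EAT-10, EORTC H&N35 and EORTC C30 questionnaires" and assigns "linear regression analyses for continuous variables", with no condition on normality. It presents these regressions as additional analyses of the between-group differences. The same section says of the economic evaluation that "95% confidence intervals will be based on bootstrapping". For the primary outcome, section 10.1 says "The endpoints complications and toxicity will be dichotomized" and "For analysis of between-group differences in the primary outcome, a logistic regression analysis will be performed".

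**The concern.** A between-group difference needs an interval that shows how precisely it is estimated. A range runs from the smallest to the largest observation. It says how varied the patients are and nothing about how well the difference between arms is known. The protocol names it as an acceptable companion to an effect estimate.

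Two things are at stake for the continuous secondary outcomes, taken here to be the questionnaire scores:

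- A reader given a median difference with a range cannot judge whether the data exclude a relevant benefit or harm.
- The p-value for the same outcome would come from linear regression, which concerns a mean difference. Estimate and test would then describe different quantities, and the protocol does not say which is the reported effect.

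Section 10 also plans multiple imputation. A range supplies no standard error to combine across imputed data sets.

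**Working it through.** The plan states no figure on this point, so there is none to reproduce. The 61 patients per arm in section 4.4 were derived for the binary primary outcome and serve here only as a realistic group size. The protocol gives no standard deviations or score distributions, so every shape below is an assumption.

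**1. Does a range measure precision?** Assume an EAT-10-like score: exponential with mean 8, rounded and capped at 40. The second column is the simulated average range in one sample of n patients (500 samples each). The third is the approximate width of a 95% confidence interval for the mean difference with n per arm, 2 × 1.96 × SD × √(2/n). It takes SD = 8, because an exponential has SD equal to its mean; the cap lowers this slightly.

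| n | Average range | 95% CI width |
|---|---|---|
| 20 | 27.5 | 2 × 1.96 × 8 × √(2/20) = 9.9 |
| 61 | 34.6 | 2 × 1.96 × 8 × √(2/61) = 5.7 |
| 122 | 37.7 | 2 × 1.96 × 8 × √(2/122) = 4.0 |
| 500 | 40.0 | 2 × 1.96 × 8 × √(2/500) = 2.0 |

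The range widens towards the limit of the scale as information accumulates, while the confidence interval narrows. Reading the word as interquartile range would not help. For this exponential shape it is 8 × ln 3 = 8.8 whatever the sample size.

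**2. Do the two contrasts estimate the same thing?** For an exponential score the median is ln 2 = 0.69 times the mean. A mean difference of D therefore appears as a median difference of 0.69 × D. Both are legitimate, but a regression p-value belongs to the first.

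**3. How often would the median route arise, if normality governs it?** Rejection rates of the Kolmogorov-Smirnov test with Lilliefors correction at 5%:

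- 61 patients, 1,000 samples: exponential 98%; seven-level 0–100 scale 100%; lognormal with sigma 0.5, 78%.
- 122 patients pooled, 1,500 samples: lognormal with sigma 1, the EAT-10-like score and a four-level item, 100% each; normal data 3.3%.

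For bounded, skewed questionnaire scores the median route would be the usual one under that reading.

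**4. Is a valid interval available without the normality test?** Coverage of the ordinary 95% t-interval for the mean difference, with 61 per arm, no true effect and 4,000 samples:

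- normal: 95.2%
- lognormal, sigma 1: 95.6%
- EAT-10-like: 95.3%
- four-level item: 95.4%

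The planned regression, which reduces to this comparison when unadjusted, gives a sound interval even where normality is clearly violated.

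**The case against.** **The normality test is tied only to presentation.** This stands. A reader might infer that the Kolmogorov-Smirnov result decides whether an effect is a mean difference with a confidence interval or a median difference with a range. The text does not say so. Normality is, however, the only criterion that the paragraph gives for choosing mean or median. If that inference is refused, the sentence offers two contrasts and two intervals with no selection rule. The range is a wrong companion to a treatment difference either way.

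**Linear regression applies whatever the normality result.** This also stands. A reader might infer that skewed outcomes are left with no valid interval at all. They are not, because section 10.2 is unconditional and step 4 shows that the resulting interval performs well. The defect lies in the section 10 contrasts, which remain a separate set of reported effects.

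**Outcomes might switch between mean and median from visit to visit.** This is tempting, but poorly supported. If normality is rejected in 98% to 100% of samples, there is almost no switching. Only milder shapes, such as the one rejected in 78%, could produce it, and no score distribution is given.

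**A median difference can stand beside a regression coefficient as description.** True. A mismatch arises only if the median difference is presented as the effect that the p-value tests, and the protocol does not settle this.

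**The interval for a median contrast is detail for an analysis plan.** That would answer an omission. Here the protocol states an alternative, and the alternative is unsuitable.

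**Conclusion.** The concern holds as a minor fault of wording and reporting. Section 10 accepts a range as an alternative to a 95% confidence interval for between-group differences, and a range cannot do that job. This conclusion needs no distributional assumption; the simulations only illustrate it.

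The reach is limited to continuous secondary outcomes, chiefly the EAT-10 and EORTC scores. The dichotomized primary outcome, the Cox analyses of recurrence and survival, and the bootstrapped economic evaluation are unaffected. No effect on power, type I error or sample size has been shown. How often a median with a range would actually be reported rests on assumed score shapes and on the inferred link to the normality test.

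**What to change.** In section 10:

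- Delete the bracketed alternative of ranges.
- State that the reported between-group effect for each continuous outcome is the mean difference from the planned linear regression with its 95% confidence interval (bootstrap or robust where the data are skewed), whatever the normality test shows.
- Keep medians and interquartile ranges as within-group description only.
- If a median difference is also shown, give it a bootstrap 95% confidence interval.

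The cost is wording and minor analysis work. Bootstrapping is already planned for the economic evaluation, and the sample size and data collection do not change.

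### Protocol section 10 treats observed-data checks, including Little's MCAR test, as a test of MAR and makes Heckman regression depend on the answer

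*Protocol*

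**What the plan says.** The rule stands in the general part of section 10, with no endpoint exempted, and has three steps.

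1. Main method: "Missing values will be handled using multiple imputation, assuming that there is only missingness at random".
2. Check: "The missingness at random assumption will be tested by exploring patterns of missing data using missingness patterns plots and missingness indicators". To these the protocol adds Little's MCAR test, the only formal test it names. No significance level is given, and nothing says how the three tools combine into a verdict.
3. Consequence: "If the missingness at random assumption had been violated, we will perform Heckman regression".

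Dropout falls under this rule, because the same section states: "Loss of follow-up because participants decide to stop the study is in our opinion not an intercurrent event but a 'missing data' problem".

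The outcomes it covers are of three kinds. For the primary outcome, section 10.1 says "The endpoints complications and toxicity will be dichotomized" and "a logistic regression analysis will be performed". Section 10.2 assigns Cox models to recurrence and survival, and linear regression to continuous outcomes. Under section 8.1.2 the quality-of-life questionnaires run from baseline to 24 months after last treatment.

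**The concern.** MAR means that, given what was observed, missingness does not depend on the values that were not observed. Pattern plots, missingness indicators and Little's test see only observed values. They can show that missingness is related to observed variables, which is evidence against MCAR. They cannot show whether it also depends on the unseen values.

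A finding that missingness relates to observed data does not speak against MAR imputation. It is the situation for which MAR imputation is designed. If that finding is read as a MAR violation, the plan moves to a selection model for MNAR data without evidence of MNAR. If the checks look clean, the plan provides no MNAR analysis at all, although MNAR has not been excluded. In both directions the choice of method follows a check of a different hypothesis and is made after the data have been seen.

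**Working it through.** The protocol states no figure on this point, so there is none to reproduce. The check has three parts.

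**1. What Little's test measures.** Take a baseline score X seen in everyone and a later score Y missing in some. The maximum-likelihood mean of Y is the observed mean of Y shifted along its regression on X. The Y term therefore drops out of Little's statistic, leaving

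d² = [n_m × n_o / n] × (mean X in missing − mean X in observed)² / var(X), on 1 df,

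where n_m and n_o are the numbers with Y missing and observed. In this layout the test is a comparison of baseline scores between dropouts and completers. It carries no information on the missing Y.

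**2. How often it rejects when MAR is true.** Inputs from the protocol: 128 patients, 5% dropout, 61 per arm = 122 (section 4.4). Assumptions: 5% test level; odds of missingness multiplied by 1.5 or 2 per SD of X; 10% and 30% missing as larger rates. As an approximation, the standardised difference in X equals the log odds ratio, so

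λ = [n_m × n_o / n] × (ln OR)², and rejection ≈ P(Z > 1.96 − √λ).

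At 5% of 128: n_m = 6.4, n_o = 121.6, and 6.4 × 121.6 / 128 = 6.08.
- OR 1.5: λ = 6.08 × 0.405² = 1.00, √λ = 1.00, P(Z > 0.96) ≈ 17%.
- OR 2: λ = 6.08 × 0.693² = 2.92, √λ = 1.71, P(Z > 0.25) ≈ 40%.

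At 10% of 122: 12.2 × 109.8 / 122 = 10.98.
- OR 1.5: λ = 1.80, √λ = 1.34, P(Z > 0.62) ≈ 27%.

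At 30% of 122: 36.6 × 85.4 / 122 = 25.62.
- OR 2: λ = 12.3, √λ = 3.51, P(Z > −1.55) ≈ 94%.

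Simulation of the same two-variable set-up agrees closely:

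| Missing | OR 1.5 | OR 2 |
|---|---|---|
| 5% (planned) | about 15–17% | about 38% |
| 10% (assumed) | 26% | 59–66% |
| 30% (assumed) | 50% | 92% |

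The spread at 10% and OR 2 depends on whether 10% is the overall rate or the rate at the average baseline score.

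**3. Whether it rejects more often under MNAR.** A second simulation used six visits, as for the questionnaires, with n = 122, correlation 0.6 between visits and monotone dropout. Dropout depended on the last observed score (MAR) or on the current unseen score (MNAR), with assumed log-odds slopes of 0.7 / 1.0. Rejection at the 5% level:

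| Nominal dropout | MCAR | MAR | MNAR |
|---|---|---|---|
| 5% | 5% | 17% / 43% | 12% / 18% |
| 15% | 4% | 41% / 84% | 16% / 38% |
| 30% | 4% | 71% / 98% | 29% / 63% |

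Realised dropout ran somewhat above nominal where it depended on scores (6.1–7.7% in the 5% row). In every matched setting the test rejects more often under MAR, where imputation is valid, than under MNAR. At nominal 5% dropout it stays silent in 88% / 82% of the MNAR trials (100 − 12, 100 − 18).

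**The case against.** Several stronger readings are tempting, and the text does not support them.

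- *Every rejected Little's test switches the analysis.* Section 10 lists three tools, gives no cut-off and nowhere says that rejecting MCAR counts as violating MAR. MAR dropout can trigger the change; the rejection rates above are not switching rates. The other two tools share the same limit, however, so combining them does not rescue the check.
- *Heckman regression replaces imputation.* This is the natural reading of a consequence that follows a violated assumption, but the sentence does not say "instead of"; an added analysis is compatible with it.
- *The plan never considers MNAR.* A Heckman model is an MNAR model. The fair complaint is that it is reached only through a check that cannot detect MNAR.
- *Heckman regression is unusable here.* The classical model assumes a continuous outcome with normal errors. It does not match the binary primary outcome or the Cox-modelled outcomes, but it can apply to the continuous questionnaire scores, where most missing data are likely. Selection models for binary outcomes also exist. The selection equation and its variables may properly be left to an analysis plan, so their absence is not counted.
- *The primary result is at serious risk.* Complications and toxicity are recorded in routine care within 30 days of surgery, or at 6 and 12 weeks after the start of (chemo)radiotherapy (section 8.1.1). Planned dropout is 5%, about six of 128 patients (0.05 × 128 = 6.4), and section 8.5 replaces withdrawals beyond that.

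What remains is that the protocol itself names the wrong check and ties a consequence to it. An analysis plan could add detail, but it would have to contradict the protocol to put this right.

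**Conclusion.** Wrong as written; should-fix. The rule cannot detect the violation it is meant to detect, and its one formal test tends to reject when MAR imputation is valid. That part is logical and rests on no assumed figure.

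The size is illustrative. With a 5% test level and an assumed OR of 1.5 to 2 per SD, Little's test rejects under true MAR in about 15–38% of trials at the planned 5% dropout. At 10–30% missing it rejects in about 26–92%; that range is an assumption more relevant to the 24-month questionnaires, which withdrawn patients no longer complete (section 8.6). No bias in a treatment effect has been estimated, and alpha, power and the sample size are unaffected. A reader might take the upper figures as the chance that the primary analysis is changed. They are not: they belong to higher missingness than the protocol plans for, and to one of three inputs to an undefined decision.

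**What to change.** Rewrite the missing-data paragraph of section 10:

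- Delete the test-and-switch rule and the statement that MAR will be tested.
- Keep multiple imputation under MAR as the fixed main analysis.
- Keep the plots, indicators and Little's test for description only, and describe Little's test as a test of MCAR.
- Pre-specify an MNAR sensitivity analysis that is run whatever any test shows, for example delta-adjusted or tipping-point imputation by arm. For the binary primary outcome, this can vary the missing patients in each arm from all non-events to all events.
- If wanted, retain a Heckman model as an additional sensitivity analysis for the continuous questionnaire scores.

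With no test-driven step, the rate of wrongly prompted changes under MAR is zero by construction. The cost is one paragraph and a little more programming.

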### 10.1 Primary study parameter(s)

The primary outcome will be adverse events (intra- and postoperative complications and (chemo)radiotherapy toxicity). Relevant complications include hemorrhage, infection and wound healing disorders including dehiscence and fistula. Complications will be measured within 30 days after surgery using the Clavien-Dindo classification and evaluated during hospital stay and planned and unplanned outpatient visits [22]. Clavien-Dindo grade  $\geq 2$  complications will be deemed clinically relevant. Toxicity will be evaluated using the Common Terminology Criteria for Adverse Events (CTCAE), version

4.0, 6 and 12 weeks after the start of (chemo)radiotherapy. The following domains are scored within the CTCAE: xerostomia, taste, throat pain, oral pain, general pain, dysphagia, hoarseness and mucositis. Clinically relevant toxicity will be defined as CTCAE toxicity grade  $\geq 3$ , irrespective of the mentioned domains.

For analysis of between-group differences in the primary outcome, a logistic regression analysis will be performed. The endpoints complications and toxicity will be dichotomized. In case of unbalance between the intervention and the control group, adjusted logistic regression analyses will be performed. A  $p$ -value  $< 0.05$  will be considered as statistically significant.

Subgroup analyses will be performed using the following variables:

- (intended) type of treatment (surgery versus (chemo)therapy)
- Subsite (larynx versus hypopharynx versus oropharynx versus oral cavity)
- Skeletal muscle mass (LSMI in  $\text{cm}^2/\text{m}^2$ )
- Duration of nutritional prehabilitation intervention
- Number of dietetic consultations
- Dietary intake using 24-hour recall

These variables will be added to the regression analyses

